### Schedule of Intervention

After obtaining informed consent the research assistant will gather residents' demographic information and measure residents' baseline mobility, function, and health-related quality of life in both the intervention and control groups (see Figure 1). The extent of baseline measurement is limited because of the frailty of this population and the likelihood of attrition during the study period. After baseline measurement the mobility intervention will be introduced exclusively to residents in the intervention group. Resident outcomes will be measured for both the intervention and comparison groups at three months and six months.

### Procedure

As the first residents are recruited from each intervention facility we will introduce the sit-to-stand intervention to the intervention facilities on the units where the residents reside. A nurse educator contracted for the study will deliver 20 minute education sessions on the sit-to-stand functional activity to as many health care aides as possible who are working on both day and evening shifts. These 20 minute sessions will be offered between 8 and 32 times depending on the size of the intervention facility. During these small group education sessions we will: a) describe the potential rationale for the sit-to-stand activity; b) provide standardized instruction and practice of the activity; and, c) illustrate how to document resident participation with the sit-to-stand activity. Following the education sessions health care aides will begin to facilitate the sit-to-stand activity with residents in their care who have been recruited to the study. Our pilot study demonstrated that health care aides require encouragement at regular intervals to consistently integrate the sit-to-stand activity into their daily routine. Thus we have included knowledge translation interventions that were tested in the pilot study to optimize the likelihood that residents in the treatment group will perform the sit-to-stand activity. In the first month the nurse educator will return to the intervention facilities to converse with the health care aides about their experiences with the sit-to-stand activity and to facilitate problem-solving around any barriers that they may have encountered. In the second month a set of reminders will be introduced including: a) prominently posting the names of resident participants where the change of shift occurs; b) affixing a colourful sticker to residents' bedroom doors and beside their beds; and, c) marking with a sticker the usual documentation flowsheets where the health care aides record residents' shift-to-shift responses to the exercise. During the third month 20 minute problem solving sessions with health care aides will be conducted to identify barriers to completing the sit-to-stand activity and to suggest ways to overcome them. The next month a poster and small handouts that summarize the discussion and problem-solving sessions will be posted on the treatment units and distributed to the health care aides. Each month a different approach will be taken to heighten the awareness of the health care aides about the importance of continuing to integrate the sit-to-stand activity into the residents' activities of daily living.

Health care aides will be invited to participate in an in-person, 30 minute interview pertaining to a specific resident if they have been permanent staff members in the facility and have been assigned to work directly with the resident in the past week. Although we considered blinding the research assistant to the intervention this is not possible to maintain because residents and health care aides will undoubtedly refer to the sit-to-stand intervention at some point during their contact with the research assistant. To minimize possible bias the research assistant gathering the outcome data will be independent of the nurse educator who will introduce the mobility intervention to the intervention group. The research assistant will not have access to data that were collected during the previous round of assessments and are unlikely to recall residents' precedent scores. The research assistant will assess all residents for the duration of the study unless unavailable; when the research manager will perform this duty. Therefore inter-rater reliability between the research assistant and the research manager will be assessed at the beginning, middle, and end of data collection.

The extent to which resident participants in the intervention group are exposed to the sit-to-stand activity will be measured using daily *documentation flowsheets *which are part the residents' health record. Managers expect these flowsheets to be completed by health care aides at the end of every day and evening shift. The precise method of incorporating the documentation of the sit-to-stand activity will be tailored to the existing flowsheets in the intervention group facilities. Experience from the pilot study demonstrated that this usual method of documenting personal care using a flowsheet can be an effective and efficient means to assess the sit-to-stand activity adherence of both the health care aides and the residents. We will use this usual documentation as a research data collection tool to minimize the response burden for health care aides. The research assistant will conduct spot checks to compare health care aide performance of the sit-to-stand activity with what they record on the flowsheets. The flowsheets will be collected monthly for the duration of the study.

The frequency and intensity of practicing the sit-to-stand activity will be abstracted from the flowsheets every month in the intervention facilities. The number of occasions per month that health care aides document that the functional activity is completed will be the measure of the frequency. The mean number of sit-to-stands completed on each occasion will be the measure of performance intensity. If after one month it is apparent that the residents in the intervention group are not performing the sit-to-stand activity at least once a day then we will conduct brief interactive education sessions with the health care aides to review the procedure for the sit-to-stand activity and the documentation process and to identify strategies to overcome any reported barriers.

## Measures

We are interested in functional activity which, according to the International Classification of Functioning, Disability and Health [55] framework, involves the execution of tasks or actions at the level of the whole human being in the daily life of the individual; therefore, we will measure functional outcomes rather than balance and strength which more narrowly focus on body functions and structure.

### Outcomes

#### Mobility

The sit-to-stand action is a functional activity that has been incorporated into a number of mobility measures including the time to rise without using arms, time for 5 sit-to-stands, time for 10 sit-to-stands, and the number of sit-to-stands completed in 30 seconds. We have chosen to measure mobility using the number of sit-to-stands in 30 seconds because in the frail nursing home population many residents must use their arms to stand [10,38,47,48] and may be unable to complete more than one sit-to-stand. This mobility assessment will be completed by a research assistant using a stopwatch and standard armchair with a standard height of 42 cm. Residents will be instructed to stand up and sit down as many times as possible until they are asked to stop after 30 seconds. In a group of community-dwelling older adults aged 66 to 97 years [47], researchers found evidence for test-retest reliability, criterion validity (comparing the chair stand performance to a measure of lower body strength), and discriminant validity (comparing performance in different age and physical activity groups) with the 30-second sit-to-stand test.

#### Function

The Functional Independence Measure (FIM) is an 18-item instrument which assesses the amount of assistance required to complete basic activities of daily living using a 7-point scale graded from 1 (dependent) to 7 (independent) [56-58]. The FIM includes motor (self-care, sphincter control, transfers, locomotion) and cognitive (communication and social-cognition) subscales. The 18 individual items are totalled to produce a score ranging from 18 to 126. Originally designed with rehabilitation populations in mind [57], the reliability and validity of the FIM has been assessed with older adults in acute care [59] and the community [58,60] with demonstrated reliability in each of these settings [61]. More recently the FIM has been used in a LTC setting [21,62,63] and has been compared with the Resident Assessment Instrument [64-68]. Eight responsiveness studies all found the physical but not the cognitive subscales to be responsive to change [59,65]. We will interview health care aides using a structured questionnaire to measure residents' functional abilities.

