The primary purpose of this study is to determine if a simple mobility innovation (the sit-to-stand activity), implemented within the context of routine care activities of health care aides, can maintain or improve the mobility, function, and health-related quality of life of residents with dementia in LTC facilities.

We have selected our mobility intervention to be the sit-to-stand activity based on: a) the feasibility of integrating it into the daily practices of health care aides and residents using existing resources; b) preliminary evidence which supports integrating activity into functional situations such as dressing, toileting, or walking rather than introducing an exercise [27,34]; and, c) evidence suggesting that performance of the sit-to-stand activity may delay the well known trajectory of functional decline in LTC residents [24,32,34-38]. The sit-to-stand activity is thought to be one of the most mechanically demanding for LTC residents [39], yet it is still considered to be a low intensity exercise. Low intensity exercise has been found to improve physical performance [40,41] and activities of daily living [40,42,43] among frail older adults in LTC facilities although high intensity exercise did achieve a greater effect [40].

The benefits of implementing this simple sit-to-stand activity are seen at several levels. The intervention is low cost, does not require any specialized staff, training or equipment nor does it involve an important increase in the time required to care for residents; thus the mobility intervention possesses most of the attributes of successfully adopted innovations [44]. At the level of the health care aide and resident, standing up from a chair has the following attributes: relative advantage (does not require extensive training); compatibility (is consistent with activity in existing routines); low complexity (is a simple activity); trialability (can be easily tried and customized to individual residents); and, observability (improved mobility was visible to some health care aides during the pilot study).

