### Intervention

Health care aides will be trained to prompt residents to repeatedly stand up and sit down on four occasions during daily functional activities (twice on each of the day and evening shifts). The number of repetitions on each occasion will vary according to residents' ability and fatigue. The sit-to-stand activity is to be integrated into usual care routines such as when entering the dining room at mealtimes, while toileting, and on other occasions of regular activity. The timing and location will be at the discretion of the health care aide. Health care aides will be reminded that, as with their usual care activities, when a resident's condition deteriorates they should consult with the registered nurse or licensed practical nurse about the appropriateness of repeating the sit-to-stand activity.

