#### Dementia Specific Quality of Life

Because utility based instruments are generic measures, a measure of attributes specific to residents with dementia is also needed [76]. We have selected the caregiver version of the Quality of Life - Alzheimer's Disease (QOL-AD) instrument because it has excellent psychometric properties, is brief (generally administered in 10 minutes), and is based on a sound conceptual framework. The QOL-AD was developed to capture the domains considered important to health-related quality of life in Lawton's broad conceptual framework: the interpersonal; environmental; functional; physical; and, psychological domains [77,78]. The 13 items including physical health, energy, mood, living situation, memory, family, marriage, friends, self as a whole, ability to do chores around the house, fun, money and life as a whole scored on a 4-point Likert scale ranging from 1 (poor) to 4 (excellent). Total scores range from 13 to 52 with 6 points on the QOL-AD scale equivalent to 1 standard deviation. The instrument has demonstrated responsiveness to change [79,80] and good evidence of reliability (coefficient α = 0.87; ICC = 0.92) and validity [80-83]. Caregiver ratings on the QOL-AD were not correlated with various levels of the person with dementia's cognitive functioning. Criterion related validity was demonstrated with Pearson correlation coefficients for measures of behavioural competence, psychological status, physical function and interpersonal environment [82,84]. Some individual item scores for the person with dementia do not correlate with those of the proxy caregiver [82,84].

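### The Functional Independence Measure is scored from interviews with the staff who deliver the intervention in one arm only, and the bias safeguards do not reach them

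*Protocol article*

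**What the plan says.** **Who rates function.** Under Function, the FIM grades how much assistance a resident needs, and its source is stated: "We will interview health care aides using a structured questionnaire to measure residents' functional abilities". Under Procedure, an aide qualifies for the resident-specific interview if they are permanent staff and "have been assigned to work directly with the resident in the past week".

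**Who delivers the intervention.** Under Intervention: "Health care aides will be trained to prompt residents to repeatedly stand up and sit down on four occasions during daily functional activities". Under Procedure, education sessions that include the rationale go "to as many health care aides as possible who are working on both day and evening shifts", and prompting continues afterwards: "Each month a different approach will be taken to heighten the awareness of the health care aides about the importance of continuing". Under Control group, measurement is the only change to residents' routine in those facilities.

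**What is done about bias.** Procedure concedes that the research assistant cannot be kept blind and offers: "To minimize possible bias the research assistant gathering the outcome data will be independent of the nurse educator". It adds that the assistant will not see the previous round's data and that reliability between the assistant and the research manager will be checked three times. Spot checks compare what aides do with what they enter on the flowsheets.

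**The other outcomes.** For dementia-specific quality of life: "We have selected the caregiver version of the Quality of Life - Alzheimer's Disease (QOL-AD) instrument". The article does not say whether that caregiver is an aide or a relative, and it names no respondent for the HUI2/3. Under Mobility, the research assistant administers the 30-second test with a stopwatch and a standard chair.

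**The concern.** The plan treats assessor bias as a question of who conducts the interview. For the FIM the judgement being recorded is the aide's. In one arm that aide belongs to a workforce that has been told why the activity should help, asked to carry it out, and reminded of its importance month after month. In the other arm the aide has had no such contact. Expectation in the rater is therefore aligned with the group being compared. That produces a systematic difference rather than noise, and neither covariate adjustment nor intention-to-treat analysis can remove it.

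Function is one of the three domains in the research question, and Data Analysis tests the FIM in the same way as the other outcomes. A positive FIM result could be read as a benefit on function when part or all of it is a change in how aides rate.

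**Working it through.** **Step 1: set the safeguards against the source of the FIM score.**

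| Measure in the protocol | Whom it constrains | Does it address aide expectation? |
|---|---|---|
| Research assistant independent of nurse educator | Interviewer | No; it limits cueing by the interviewer |
| No access to previous-round data | Interviewer | No |
| Reliability, research assistant against research manager | Interviewer | No |
| Spot checks of flowsheets | Aide, as recorder of delivery | No; outcome ratings are not checked |
| Structured FIM questionnaire | The questions | Standardises wording, not belief |

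**Step 2: compare the informants by arm.** The eligibility rule (permanent staff, recent direct work with the resident) is the same in both arms. In intervention facilities it draws on the aides who are expected to deliver the activity. In control facilities it draws on aides with no role in it.

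**Step 3: reproduce the plan's own sample size.** Inputs from Sample Size: difference 2, SD 3.5, two-sided alpha 0.05, power 0.80.

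n per group = 2 × (1.960 + 0.842)² × 3.5² / 2² = 48.1, rounded up to 49, as stated. The t-test power at 49 per group is 0.80.

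**Step 4: illustrate what a rating shift would do.** Assumptions: no true effect, 49 evaluable residents per arm, two-sided alpha 0.05, a two-sample t-test, independent residents (clustering by facility ignored), and an average rating shift of b SD in the intervention arm only. The standard error of the difference, in SD units, is √(2/49) = 0.202, so the expected test statistic is b / 0.202.

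| Assumed shift b (SD) | Expected statistic | Probability of p < 0.05 |
|---|---|---|
| 0 | 0 | 5% |
| 0.10 | 0.49 | 8% |
| 0.25 | 1.24 | 23% |
| 0.33 | 1.63 | 37% |
| 0.50 | 2.47 | 69% |

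A normal approximation gives 24% and 70% for shifts of 0.25 and 0.50 SD.

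**Step 5: what these shifts mean on the scales.** The article gives no SD for the FIM, so they cannot be turned into FIM points. For the QOL-AD it equates 6 points with 1 SD, so 0.25 SD is 1.5 points and 0.5 SD is 3 points. That conversion matters here only if aides are the QOL-AD respondents.

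**The case against.** **The informant rule has a purpose.** Rating how much help a resident needs requires someone who has recently given that help, and the rule is applied alike in both arms. This stands: the rule is not itself a fault, but it does not remove the difference in expectation between arms.

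**Some measures do bear on the interview.** A structured questionnaire and an interviewer independent of the nurse educator limit prompting of the aide. That also stands, but neither changes what the aide believes.

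**The size of the bias is not documented.** Correct. Nothing in the article gives its size or even its direction. The probabilities above are a power curve at assumed shifts, and 0.5 SD averaged over all residents is not a small shift.

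**Stronger readings that the article does not support.**
- A reader might infer that two of the three domains, function and quality of life, rest on ratings by the intervention's deliverers. The 30-minute aide interview is the only proxy interview described and could hold all three instruments, but that does not show that it does. The full protocol may name the respondents.
- A reader might take the pilot as evidence that aides imagine improvement. Background says only that improved mobility was visible to some aides, and does not suggest that they were mistaken.
- A reader might conclude that the whole study can find a benefit where none exists by this route. The 30-second test is performed by the research assistant, so aide rating does not touch it.

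**Conclusion.** The point holds for the FIM. Aides supply the scores, only intervention-facility aides are trained and prompted, and the stated safeguards act on the interviewer. As written, the plan cannot separate a FIM effect from rater expectation.

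For the QOL-AD and HUI2/3 the point is conditional: it applies if aides are the respondents, which the article leaves open. If relatives answer, it narrows to the FIM and still stands there.

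The size is unknown. The range of about 23% to 69% against a nominal 5% rests on assumed shifts of 0.25 to 0.5 SD, 49 per arm, no true effect and independent residents. It also uses a simple t-test rather than the planned repeated-measures analysis of covariance. It shows that a moderate shift would be enough to mislead; it does not estimate what will happen. Because the outcome that drives the sample size is unaffected, this is a change that should be made, not one that invalidates the study.

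**What to change.** 1. **Supportive check.** Under Covariates, RAI 2.0 records are already to be acquired for the quarters nearest baseline, 3 months and 6 months. Extract the functional (activities of daily living) items from the same records and state in advance that they will be analysed by group as a supportive comparison for the aide-rated FIM. State too that these records come from unblinded facilities and only approximate the visit dates, so they reduce the problem without removing it.
2. **Informants, in both arms alike.** Use the same informant at all three visits where possible. At each interview record whether the informant attended a sit-to-stand session and whether they delivered the activity to that resident. Do not pick the least-involved aide in the intervention arm only. That would create a new measurement difference between arms, and it would clash with keeping the same informant from baseline, when involvement with that resident is not yet known.
3. **Conclusion.** Rest the main efficacy conclusion on the 30-second test. State that a FIM effect, or an effect on any other aide-rated outcome, that the RAI data do not support cannot be separated from rater expectation.

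**Cost:** a few extra fields from records already requested, two more interview items, and a more cautious conclusion on function. No additional visits are needed.

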#### Health-Related Quality of Life

The Health Utilities Index Mark 2 and 3 (HUI2/3) is a generic health-related quality of life questionnaire based on two generic multi-attribute preference-based systems: the HUI2 and the HUI3 [69]. Interview administered versions of the HUI2/3 can typically be completed in 3 minutes [70] although other researchers report that it takes 15 to 20 minutes to administer the HUI2 to frail older adults [71]. The HUI2 assesses capacity on six dimensions (or attributes) of health status: sensation (vision, hearing, and speech), mobility, emotion, cognition, self-care, and pain. The HUI3 assesses capacity on eight attributes: vision, hearing, speech, ambulation, dexterity, emotion, cognition, and pain with each attribute consisting of five or six levels ranging from normal to severely impaired function. The HUI3 may be less prone to floor effects than the HUI2, and the HUI3 has a greater capacity to measure a wider range of utility scores than does the HUI2. Together the HUI2 and HUI3 provide complementary and clinically relevant information for LTC residents with dementia. Both have been used in samples of people with dementia [72-75]. When the HUI2 was administered to frail older adults and caregiver proxy respondents of people with dementia there was evidence of discriminant validity [76], construct validity [74] and responsiveness to decline but not responsiveness to improvement [72,74]. A change of 0.03 or more in overall HUI scores is considered clinically important as is a change in level within any of the HUI attributes [71]. The HUI2/3 was chosen over other health-related quality of life measures because its widespread use facilitates the interpretation of results and allows comparisons.

